### Substudy 2: Patients’ Perspective (Qualitative)

This substudy aims to explore how patients perceive and experience IN interventions, as well as their level of satisfaction with the implementation of IN. The primary focus is an in-depth examination of individual perceptions to gain a more nuanced understanding of how IN interventions are received and experienced from the patient’s perspective.

#### Study Design

In this substudy, we will use a qualitative approach, and semistructured interviews will be conducted.

#### Participants

Patients who received IN interventions during their inpatient stay will be invited to participate in interviews after discharge. Additional inclusion criteria are age 18 years or older, capacity to provide informed consent, and provision of written informed consent. Exclusion criteria include pronounced cognitive deficits, an imminent dying process, and limited ability to communicate (eg, insufficient language proficiency).

Purposive sampling will be used to identify and select cases that are rich in information [59]. Participants will be selected to ensure variation in factors such as sex, age, and number of IN interventions received, thereby capturing a wide range of perspectives on the implementation of IN. A minimum of 12 interviews is initially estimated to capture sufficient diversity of patient experiences to address the research questions [60]. However, sampling will be flexible and will continue until thematic saturation is reached, defined as the point at which no new significant themes, concepts, or insights emerge from the data.

#### Data Collection

During their hospital stay, patients will be informed verbally and in writing by study staff. After discharge, they will be contacted by telephone to confirm their interest in participating and to clarify their preferred format and scope of the interview. Upon providing written informed consent, participants will be interviewed online, by telephone, or in person, according to their preference. A semistructured interview format guided by an interview guideline will be used. Each interview will last approximately 45 minutes and will be audio recorded. In addition, the interviewer will take structured notes using a standardized interview protocol to capture relevant contextual details for later analysis. To support sample characterization, the following variables will be recorded: age, sex, marital status, number of children, occupation, and number and type of IN interventions received.

#### Interview Guideline

The interview guideline was developed based on research interests, following the principle of “collecting, checking, sorting, subsuming” [61], and with consideration of CFIR [57]. The guideline will address the following four main topics: (1) previous experience with and use of CIM and IN, (2) perception and experience with IN at both the physical and psychological levels, (3) satisfaction with the implementation of IN during the hospital stay, and (4) perspectives on the future use of IN, including potential integration into everyday life. At the end of the interview, participants will also be invited to provide additional comments or reflections.

#### Data Analysis

Audio recordings will be transcribed according to the simple transcription guidelines proposed by Dresing and Pehl [62]. Any personally identifiable information will be anonymized to ensure data protection. Data will be analyzed using structuring qualitative content analysis as proposed by Kuckartz [63], which combines deductive and inductive category development. Deductive categories will be derived from the research questions and CFIR, while additional inductive categories will emerge from the data. The coding system will be redefined iteratively throughout the analysis process. To enhance credibility and reliability, at least 2 researchers will be involved in coding and interpretation. Initially, a subset of transcripts will be coded independently, and the resulting codes and themes will be compared and discussed to reach consensus. The remaining data will then be coded through a consensus-driven approach by the research team. Data analysis will be performed using MAXQDA (VERBI Software). Upon completion of the analysis, all audio files will be permanently deleted to ensure compliance with data protection regulations.

### Substudy 3: Relatives’ Perspective

Relatives are considered key stakeholders in exploring the feasibility and relevance of transferring low-threshold IN interventions into the home care setting after hospital discharge. The aim of this substudy is to examine relatives’ perspectives on the use of, attitudes toward, and interest in CIM, as well as their perceptions of IN for inpatients.

#### Study Design

In this substudy, we will conduct an anonymous, cross-sectional survey using a quantitative descriptive research design.

#### Participants

The survey will include all relatives of patients who receive IN interventions as part of the IMPLEMENT-UKU project at the hospital. Eligibility criteria for participation are age 18 years or older, sufficient language proficiency, being a relative of a patient received IN interventions, and provision of informed consent.

#### Data Collection

Relatives will be invited to participate in the survey through information flyers and direct contact by nurses involved in the project, who will provide verbal and written information about the study. Participation in the survey is possible using a paper-based questionnaire or a web-based version. The online survey is administered using the Unipark platform (Tivian XI GmbH). Participants will access the questionnaire using a survey link or QR code, and responses will be submitted anonymously.

#### Study Outcomes

The questionnaire includes the following domains: sociodemographic data (2 items), caregiving support (3 items), definition of CIM (2 items), previous use of CIM (12 items), interest in using CIM (12 items), perception of IN at the hospital (5 items), involvement of relatives in project implementation (2 items), and space for additional comments (1 item).

#### Data Analysis

Missing data will be assessed in terms of frequency and distribution across all variables. Cases with missing values will be excluded using listwise or pairwise deletion, as appropriate. Descriptive statistical methods will be used to analyze the data. Depending on the level of measurement, absolute and relative frequencies, means, SDs, and medians will be calculated.

### Substudy 4: Medical and Nursing Staffs’ Perspective

The involvement of health care professionals, including nursing and medical staff on the participating wards, is essential for capturing implementation processes and complementing the perspectives of patients who have received IN interventions. The objective of this substudy is to explore the facilitators and barriers to the implementation of IN from the perspective of health care professionals, as well as their perceptions of its effects and its impact on routine clinical practice.

#### Study Design

In this substudy, we will use a qualitative approach, and semistructured interviews will be conducted.

#### Participants

Nursing and medical staff from the wards participating in the IMPLEMENT-UKU project, as well as the integrative nurses delivering the IN interventions, will be invited to participate. Additional eligibility criteria include age 18 years or older, sufficient language proficiency, employed on a participating ward or within the project, and provision of informed consent.

A purposive sampling strategy will be used to identify and select participants who can provide rich and relevant information [59]. The sampling approach will aim for maximum variation in key characteristics such as age, professional background, and years of employment, to capture a broad range of perspectives. This study aims to conduct a minimum of 12 interviews to collect sufficient diverse perspectives to address the research questions [60]. Sampling will continue until thematic saturation is reached, defined as the point at which no new significant themes, concepts, or insights emerge from the data.

#### Data Collection

Potential participants will be contacted through personal communication, mail, or telephone. Ward managers will serve as gatekeepers during the recruitment process. Nurses and physicians will be informed verbally and in writing by the study staff before the interview. Upon providing written informed consent, interviews will be conducted online, by telephone, or in person, according to the participant’s preference. The interviews will be conducted using a semistructured guideline. Each interview will last approximately 45 minutes and will be audio-recorded. Additionally, the interviewer will take structured notes using an interview protocol to capture relevant contextual aspects for later analysis. The sample description will include age, sex, profession, years of professional experience, and additional CIM training.

#### Interview Guideline

The interview guideline was developed based on research interests, following the principle of “collecting, checking, sorting, subsuming” [61] and with consideration of CFIR [57]. The semistructured interview with nursing and medical staff will cover the following key topics: (1) the process of implementing the IN project, (2) perception and experience with IN on the ward, (3) support and enabling factors to IN implementation, (4) impediments and barriers to IN implementation, and (5) suggestions for future improvements. Participants will also be invited to share additional comments and reflections at the end of the interview.

#### Data Analysis

Audio recordings will be transcribed using the simplified transcription guidelines outlined by Dresing and Pehl [62]. Any information that could reveal participants’ identities will be anonymized during this process. Qualitative data will be analyzed using structuring content analysis according to Kuckartz [63], which combines both deductive and inductive category development. Deductive categories will be derived from the study’s research objectives and CFIR, while additional inductive categories will be identified directly from the data. The category system will be refined iteratively during the coding process. A subset of data will be independently coded by at least 2 researchers, after which the code systems and thematic patterns will be compared and discussed. The remaining data will be coded collaboratively using a consensus-driven approach. Analysis will be conducted using MAXQDA (VERBI Software). In accordance with data protection regulations, all audio files will be permanently deleted upon completion of the analysis.

### Substudy 5: Project-Related Data

In addition to primary data sources, routinely collected data from the IMPLEMENT-UKU project will be used to complement the analysis and assess the feasibility and real-world implementation of IN. This substudy focuses on key implementation indicators, including acceptance, study participation rate, intervention fidelity, and the number of IN visits and interventions performed. Furthermore, the analysis will support the identification of required resources and potential cost factors associated with implementation in routine care.

#### Study Design

In this substudy, we will conduct a retrospective analysis using project-related routine data.

#### Participants

The sample will include all requests for IN consultations and all patients who participated in the project during the study period.

#### Data Collection

Project-related routine documentation will serve as the data source for all IN consultation requests, as well as the corresponding IN visits and interventions. Data for participants in substudy 1 will be collected pseudonymously, while data for all other project participants will be extracted anonymously.

#### Study Outcomes

All parameters shown in Textbox 1 will be collected from project-related routine data. This includes sociodemographic and clinical data, details on IN consultation requests and rejections, records of IN visits and interventions performed, and study participation. These data will be used to analyze the acceptance rate of the IN offer, the study inclusion rate, and intervention fidelity, defined as the extent to which the interventions are delivered in accordance with the standard operating procedure (eg, duration), and to estimate the resources and costs associated with implementing IN.

Collection of project-related routine data (substudy 5).
**Sociodemographic and clinical data**
Sex, age group, ward, and diagnosis group (*International Statistical Classification of Diseases and Related Health Problems, Tenth Revision* [*ICD-10*])
**Integrative nursing (IN) consultation service**
Reason for IN consultation request, acceptance or rejection of the IN offer, and reasons for rejection
**IN visits**
Number of visits per patient, duration, notes of preliminary conversation, patient symptoms perceived or reported

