### Purpose of This Study

This evaluation study is embedded within the IMPLEMENT-UKU project and will examine the implementation of IN through a comprehensive, accompanying scientific investigation that integrates the perspectives of patients, their relatives, and hospital staff. It aims to address the following research questions: (1) To what extent can IN be implemented as intended on the participating wards, including the delivery of IN (eg, number of IN consultations, IN interventions) and its acceptance and perception among patients, relatives, and health care professionals (eg, evaluation of IN, perceptions of IN interventions)? (2) What are the key contextual factors influencing the implementation of IN, including identification of relevant contextual factors and assessment of the implementation process, such as barriers and facilitators? (3) What are the indicators of potential effects of IN at the patient level, with a focus on patient-reported outcomes (eg, well-being, quality of life, self-efficacy, and symptom burden)?

This study aligns with the research priorities outlined in the “German Research Agenda for Nursing Oncology,” particularly regarding the management of disease-related symptoms and treatment side effects, as well as the promotion of quality of life across different phases of health and disease [43].

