## Methods

### Project IMPLEMENT-UKU: Setting and Intervention

The IMPLEMENT-UKU project and its accompanying evaluation study are being carried out as a single-center initiative at the University Hospital Ulm. Within the framework of the project, patients with cancer on participating wards receive IN interventions as supportive care during their hospital stay as part of a consultation service. Figure 1 illustrates a flowchart of the patient care pathway within the project.

Patients will be referred to an initial IN consultation by nursing or medical staff on the participating wards. Referrals will be based on pertinent and acutely distressing symptoms and problems, such as restlessness, pain, or cancer-related side effects, which are relevant to care and indicate the need for supportive interventions. Following referral, patients will receive an initial IN consultation, which may be followed by additional IN visits and interventions throughout their hospital stay. During the initial IN consultation, the integrative nurse will provide information about IN, the overarching IMPLEMENT-UKU project, and the ongoing evaluation study. The first IN intervention will be conducted directly after this consultation. The number of subsequent IN visits and interventions may vary depending on patient needs and the duration of hospitalization.

Depending on each patient’s symptom burden and individual preferences, patient-tailored IN interventions will be offered alongside routine care. To ensure consistent application, these interventions will be guided by a symptom-driven IN intervention catalog (Table 1). The IN catalog was developed through an expert consensus process, drawing on external naturopathic nursing textbooks [11,12,44-47], academic literature [14,15,18,19,48], and recommendations from previous projects and guidelines [36,49-51]. To ensure intervention fidelity, standard operating procedures are available for all IN interventions.

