#### Data Analysis

Where feasible, complete case analysis will be performed; otherwise, pairwise deletion will be applied. Quantitative data will be analyzed using descriptive statistics, including frequencies, medians, means, and SDs, as appropriate. Subgroup analyses (eg, by sex, age group, diagnosis, or type of IN intervention) will be exploratory in nature. Group comparisons will be conducted using independent samples *t* tests for interval-scaled variables and chi-square tests for categorical variables. If the assumptions for parametric tests are not met, nonparametric alternatives such as the Mann-Whitney *U* test and Fisher exact test will be used. The significance level will be set at 5% (*P*<.05). Qualitative data from the open-ended text fields will be categorized using thematic content analysis.

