## Discussion

### Overview

This study outlines the protocol for mixed methods research aimed at making a theory-based contribution to the implementation of IN for inpatients and examining its potential effects at the patient level. The following anticipated findings are derived from the study’s research questions: IN visits and interventions are expected to be implemented as intended, with a moderate to high number of IN consultation requests and repeated IN visits and interventions per patient during the hospital stay. Acceptance rates among patients and staff are likely to be high, with health care professionals perceiving IN as a meaningful complement to conventional care. Contextual, structural, and organizational factors are anticipated to act as key barriers and facilitators in the implementation process. Initial results are expected to show improvements in well-being, reductions in symptom burden, and increased self-efficacy. IN interventions are anticipated to be perceived as supportive and not associated with additional burden. Patients may also report short-term subjective benefits such as enhanced vitality, a sense of warmth and strength, and feelings of calm following IN interventions.

The findings can subsequently be compared and contextualized with studies that have implemented CIM or IN in other settings, such as pediatric care [37,38,40,41,68-70] and outpatient oncology care [35,42,71,72], as well as with studies and programs offering IO for patients [33,73-75]. Situating the findings within the framework of implementation science is essential for advancing both the conceptual development and practical integration of IN into routine care [76]. This research is expected to make a substantial contribution to the implementation of IN as a service for inpatients. Furthermore, the findings will support the German Research Agenda for Nursing Oncology and help establish a scientific foundation for IN in oncology care [43].

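### Substudy 5 counts IN visits and interventions per patient but lists no length of stay, so a low count cannot be told apart from a short stay

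*Protocol article*

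**What the plan says.** All places are in the protocol article.

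- **Purpose of This Study.** The first research question asks how far IN can be implemented as intended, "including the delivery of IN (eg, number of IN consultations, IN interventions").
- **Substudy 5, introduction.** The key implementation indicators are "acceptance, study participation rate, intervention fidelity, and the number of IN visits and interventions performed".
- **Project IMPLEMENT-UKU: Setting and Intervention.** "The number of subsequent IN visits and interventions may vary depending on patient needs and the duration of hospitalization". The same section says that the first intervention directly follows the initial consultation.
- **Substudy 5, Study Outcomes.** "All parameters shown in Textbox 1 will be collected from project-related routine data". The entry for visits is "Number of visits per patient, duration, notes of preliminary conversation, patient symptoms perceived or reported". The entry for interventions is likewise a count per patient, with duration, body region, type, substances, reactions and side effects. The patient-level variables are sex, age group, ward and diagnosis group.
- **Substudy 5, Data Analysis.** "Subgroup analyses (eg, by sex, age group, diagnosis, or type of IN intervention) will be exploratory in nature". Group comparisons use t tests or chi-square tests, or nonparametric alternatives, at the 5% level. No adjustment for time in hospital is described.
- **Discussion, Overview.** One anticipated finding is "repeated IN visits and interventions per patient during the hospital stay".

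**The concern.** A count of visits has an exposure time behind it: the days on which the patient was in hospital and could be visited. The article names that exposure as one driver of the count but does not list it among the data. One or two visits may then mean a service that did not come back, or a patient who was discharged. These readings point in opposite directions for the first research question.

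The same gap affects comparisons. If diagnosis or age groups differ in length of stay, their visit counts will differ even when the service treats every patient alike on every day. The article says that its documentation allows variability in delivery to be related to patient characteristics and context. For visit and intervention counts, the listed data do not support that without the days available.

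**Working it through.** **Is length of stay collected?** Textbox 1 has five blocks: sociodemographic and clinical data, consultation service, visits, interventions, and study participation. None contains length of stay, admission date or discharge date. Duration appears twice, once as an attribute of a visit and once of an intervention. The Study Outcomes text confirms this meaning, because it cites duration as an example when defining fidelity as interventions being "delivered in accordance with the standard operating procedure (eg, duration"). No other section lists length of stay as a collected variable.

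**Simple arithmetic.** The article gives no stay, visit rate or target count, so there is no figure to reproduce. Assume one initial visit plus 0.4 further visits per remaining inpatient day.

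- 5 remaining days: 1 + 0.4 × 5 = 3 visits.
- 15 remaining days: 1 + 0.4 × 15 = 7 visits, with identical daily delivery.
- Conversely, 2 further visits in 5 days (2/5 = 0.40 per day) and 2 in 20 days (2/20 = 0.10 per day) give the same count, although the daily rates differ fourfold.

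**Simulation of a group comparison.**

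- Group size: about 20 eligible patients per month (Substudy 1, Participants) over 16 calendar months (October 2023 to January 2025, Results) gives 20 × 16 = 320, or 160 per group if split equally. With the projected 30% recruitment, 0.30 × 320 = 96, or 48 per group.
- Assumptions not in the documents: stay follows a gamma distribution with shape 2 and a minimum of 1 day. Visits are 1 + Poisson(rate × (stay − 1)), with the same rate, 0.2 or 0.4 per day, in both groups. There were 4,000 runs and a two-sided 5% level.

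Share of runs in which a t test on raw counts rejects. In each cell the first figure is for 0.2 and the second for 0.4 visits per day.

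| Mean stay (days) | 160 per group | 48 per group |
|---|---|---|
| 7 vs 7 | 4.8%, 5.3% | 4.6%, 5.8% |
| 7 vs 8.4 | 35%, 44% | 13%, 17% |
| 7 vs 10 | 88%, 95% | 39%, 49% |
| 7 vs 14 | 100%, 100% | 92%, 97% |

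Comparing further visits per remaining day instead (conditional Poisson test) rejects in 4.3% to 5.4% of runs with 160 per group and 4.5% to 5.5% with 48 per group, whatever the difference in stay. In these scenarios length of stay explains about 44% to 75% of the variance in visit counts.

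**Why the first visit must be set aside.** Every treated patient has a first visit, however short the stay. Dividing all visits by days would create a new artefact. In the example above, 3/5 = 0.60 and 7/15 = 0.47 per day differ under identical delivery. Further visits alone give 2/5 = 6/15 = 0.40.

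**The case against.** The case against has real weight.

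- **Patient needs also drive the counts.** The article names needs as well as stay, and says only that counts may vary. A reader might infer that the results will simply mirror days in hospital. The text does not support that. It supports only that the two cannot be separated with the listed data.
- **Most indicators are untouched.** A reader might infer that uptake as a whole is compromised. The acceptance rate rests on offers accepted or rejected, and the study inclusion rate and procedural fidelity have no exposure-time problem. Total visits and minutes per patient, long stays included, are the right basis for local resource totals.
- **No test of visit counts is named.** The analysis section gives generic tests and calls the subgroup analyses exploratory. It does not say that visits per patient will be compared between groups, and there is no success threshold. The confounding applies if such a comparison is made. It is not a stated confirmatory test.
- **The service is led by need and has no planned visit frequency.** A lower daily rate is therefore not in itself poorer delivery. This is a reason to report the rate beside the count, not in its place.
- **An article condenses.** Textbox 1 is not said to be exhaustive, and dates may exist in hospital records. But it goes down to body region and substances used, and is presented as the parameter list. A later analysis plan cannot adjust for a variable that was not extracted. Ward and diagnosis group allow only rough stratification.
- **The simulation builds in its answer.** Equal daily rates and unequal stays were assumed, so it shows how sensitive a raw count is, not what this study will find.

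**Conclusion.** The point holds for one of the four key indicators of substudy 5, the number of visits and interventions. The article ties that number partly to duration of hospitalization and does not list length of stay. A low count therefore cannot be separated from a short stay, and an exploratory comparison of counts between sex, age or diagnosis groups is confounded by days in hospital. How much it matters depends on how far stays differ between groups, which the documents do not say. Under the assumptions shown, with 160 per group, a gap of 7 versus 8.4 days raises the rejection rate from about 5% to 35% to 44%. The issue concerns interpretation of descriptive and exploratory results. It does not invalidate the study, but it bears on the first research question and is worth correcting.

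**What to change.** 1. Add one field to the routine-data extraction: days from first IN consultation to discharge.
2. Keep the raw counts per patient. Beside them, report visits and interventions after the first visit per remaining inpatient day, and the share with at least 2 visits among patients who stayed long enough for a second, with the cut-off stated.
3. Where groups are compared on delivery, model the count of further visits with log remaining days as offset. Poisson is the simple choice; negative binomial is safer because needs vary between patients. Patients with no remaining days contribute no exposure and are left out of this model.
4. Describe length of stay by subgroup, so that readers can judge the raw counts.

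The cost is one field for all project patients and a few table rows. It may no longer be fully achievable: data collection ended in March 2025, data verification was done by October 2025, and records of patients outside substudy 1 are extracted anonymously. If those records cannot be linked, do this for the pseudonymised substudy 1 patients and state the limitation for the rest. The Limitations section does not mention it at present.
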